#### Sample Storage

All study sites will collect, process, and store samples in local freezer storage at temperatures between − 32 °C to -80 °C in boxes or crates. The samples will be sent to the laboratory of the coordinating center in batches every 6 months. All samples can be stored for up to 30 years and must then be destroyed or disposed.

#### Data and biospecimen use in the biobank of the NCT network

Surplus biospecimen (blood and stool samples) not needed for the purposes of the LEONORA study will be transferred to the biobank of the NCT network for those study participants who provided additional informed consent for participation in this biobank. As outlined in the patient information and consent form for this biobank, they will be used for secondary medical research purposes. The aim of research in the NCT network is to understand the causes and mechanisms of the development and progression of cancer, to quickly transfer promising approaches from cancer research to the clinic and thus benefit future patients. Prior to any data access, a project with data of biobank of the NCT network needs to be approved by an ethics committee. Scientists of the NCTs and collaboration partners are allowed to ask for data access for a specific project with an ethic committee approval at the Use and Access Committee of the biobank of the NCT network. If approved, data and biospecimen will be shared in pseudonymized form.

### Biomarker measurements

#### Cultural microbiology

For detection of MDRO and recultivation of pathogens of interest, samples will be sent to the University Hospital of Cologne. Samples obtained during study conduct will be subjected to a targeted culture for detection of MDRO and pathogens of interest (Enterobacterales, non-fermenting bacteria, Staphylococcus aureus). This needs to be assessed for every included patient in the samples from day 90, and, depending on occurrence of study events after day 90 should be repeated in later samples. Samples will be subjected to selective culture using suitable media (i.e. chromagar) and subsequent isolate characterization including antimicrobial resistance testing and PCR for selected resistance genes if applicable.

In cases with detection of MDRO colonization in the day 90 samples, baseline and day 30 samples will be selected for cultural analysis in order to differentiate between newly acquired and preexisting MDRO colonization.

If there is not yet clarity about the causative pathogen, samples preceding the development of an infection may be selected to recultivate the causative pathogen from its likely endogenous origin (i.e. fecal sample). Identified bacteria will be subjected to antimicrobial resistance testing and may be selected for further characterization via whole genome sequencing.

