With 206 patients, the LEONORA trial would be the largest placebo-controlled RCT worldwide to be conducted on the efficacy of synbiotics in the prevention of postoperative complications in CRC patients. Moreover, the LEONORA trial would be the first on this topic from Germany specific for CRC patients. The only 3 previous studies from Germany included pancreatic cancer patients or heterogeneous cancer populations [19–21]. In addition, it would be the first trial worldwide looking into the effects of synbiotics on the emergence of multidrug-resistant organisms. Furthermore, stool samples will be collected to ascertain changes in microbiota composition. Due to the low case numbers and short follow-up times, all meta-analyses on cancer survival were inconclusive [11–15]. Thus, having another large trial with several years of mortality follow-up time might lead to a statistically significant pooled effect estimate for cancer survival in future meta-analyses.

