### Study endpoints

The primary endpoint of the study is the gastrointestinal function-related quality of life 90 days after surgery, as assessed by the Gastrointestinal Quality of Life Index (GIQLI) total score [26].

Secondary endpoints ascertained during interventional study phase.

GIQLI total score 30 days after surgery.GIQLI subscales 30 and 90 days after surgery: symptoms (e.g. diarrhea, flatulence and constipation), physical functions, emotions and social function subscale.Changes in GIQLI total score and sub-scales from pre-surgical visit to day 30 and 90.Low Anterior Resection Syndrome (LARS) Score at day 90 after surgery.Further quality of life total and sub-scales (EQ-5D-5 L, EORTC QLQ-C30, and EORTC QLQ-CR29) 30 and 90 days after surgery and their changes from pre-surgical visit to day 30 and 90.Fatigue scale (EORTC-FA12) and sub-scales at day 90 after surgery.Anxiety (GAD-7) at day 90 after surgery.Cost-effectiveness (costs per prevented diarrhea case) and cost-utility of the intervention (costs per quality adjusted life-year (QALY) gained, as assessed with the EQ-5D-5 L).Emergence of multidrug-resistant organisms (MDRO) until day 90.Rate of physician-documented infections (bloodstream infection (BSI), catheter-related BSI, pneumonia, surgical site infections, intra-abdominal infections, and urinary-tract infections) until day 30 and day 90.Rate of self-reported infections (upper and lower respiratory tract infections, gastro-intestinal tract infections, bladder infections, wound infections, other infections and episodes with high fever (≥ 38 °C)) until day 30 and day 90.Total rate of infection until day 30 and day 90.Antibiotics use (Yes/No and number of days) until day 30 and day 90.Rates of post-operative complications, defined as the following 4 clinical events: Initiation of antibiotic or antifungal treatment, surgical revision, new mechanical ventilation, sepsis or death until day 90.Time from CRC surgery to hospital discharge.Number and length of re-hospitalizations until day 90.Changes in the gut microbiome composition until day 30 and day 90.Concentration changes of biomarkers of inflammation and immune function in serum samples collected prior surgery and 90 days after surgery (89 proteins of the combination of the OLINK^®^ Target 48 Cytokine panel and the OLINK^®^ Target 48 Immune Surveillance panel, including, for example, interleukin-6 as well as biomarkers of systemic inflammatory response (C-reactive protein (CRP), mGPS (modified Glasgow prognostic score), HS_mGPS (high-sensitive mGPS), NLR (neutrophil-to-lymphocyte ratio), PLR (platelet-to-lymphocyte ratio), LMR (lymphocyte-to-monocyte ratio), SII (systemic immune-inflammation index), PNI (prognostic nutritional index), and NPS (neutrophil-platelet score))).Concentration changes of metabolomic biomarkers (pre-defined selection of amino acids, fatty acids, and bile acids measured with high accuracy with targeted LC-MS/MS and the total metabolome measured with untargeted LC-MS/MS, which has lower accuracy) in fecal and plasma samples collected prior surgery and 90 days after surgery.

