### Study visits

Table 2 gives an overview on the study visits and more details follow in text below the table.

**Table 2 Tab2:** Study visits of the LEONORA study

Study visit	Time point	Intervention(s) / Procedure(s)
Pre-surgery visit	Day − 13 prior surgery to day of surgery	Informed consent, randomization, 1st questionnaire, 1st fecal sample (or rectal swab) and 1st blood sample.
Post-surgery visit	Day 1–3 post surgery	Handing out of trial medication and patient diary. Start of treatment as soon as liquid diet is being tolerated for 12 weeks (84 days).
Continuous monitoring for appearance of clinical events and compliance	Day 1 – Hospital discharge	Screening for clinical events (antibiotic/antifungal treatment, surgical revision, ventilation, sepsis or death), and monitoring of regular intake of study medication daily until hospital discharge. If a clinical event is detected, information will be documented in the eCRF.
Day 30 visit	Day 28–49 post surgery	2nd questionnaire and 2nd fecal sample.
Day 90 visit	Day 87–108 post surgery	End of trial. 3rd questionnaire, 3rd fecal sample, 2nd blood sample, and collection of filled patient diary.
Month 6 follow-up visit	Day 183–218 post surgery	4th questionnaire and 4th fecal sample. Collection of data on hospitalizations, infections, cancer treatments, cancer incidence/re-occurrence and vital status at authorities and/or general practitioners/oncologists.
Year 1 follow-up visit	Day 365–400 post surgery	5th questionnaire and 5th fecal sample. Collection of data on hospitalizations, infections, cancer treatments, cancer incidence/re-occurrence and vital status at authorities and/or general practitioners/oncologists.
Year 2 follow-up visit	Day 730–765 surgery	6th questionnaire. Collection of data on hospitalizations, infections, cancer treatments, cancer incidence/re-occurrence and vital status at authorities and/or general practitioners/oncologists.

*Abbreviations:*
*eCRF* electronic Case Report Form

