On-site monitoring of documentation will not be generally conducted at all study sites. However, in case of considerable doubt regarding compliance to study protocol adherence, documentation quality or accuracy, the study coordinators may perform on-site source data monitoring using qualified personnel. During such audits, entries in the eCRF will be compared with the original source documents. The site leader will cooperate in resolving any queries or findings made during the whole monitoring process. A data monitoring committee will not be initiated because the data management team in the University Clinic Cologne, in charge of the monitoring, has enough experienced from previous studies.

The eCRF will be used to collect the following data:

General Information: Study-ID, Age, Sex, weight, height, Inclusion/Exclusion Criteria.CRC information (stage prior surgery, location (ICD-10 code)).Information on patient status (comorbidities, concomitant medication, oncological treatment regimen (chemotherapy incl. number of cycles/ radiotherapy), current location (inpatient, department, ward), known allergies against anti-infective substances, admission, readmission).Information on surgical procedure.Information on clinical events.Detection of MDRO during any local microbiological sampling.Occurrence of consecutive surgeries, including possible repositioning of stoma.Data collected at the study visits conducted while study participants are hospitalized with exception of the questionnaire data.Concomitant medication.Anti-infective treatments.

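### The endpoint is MDRO emergence up to day 90, but the culture rule finds only newly acquired colonisation still present at day 90

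*Protocol article*

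**What the plan says.** The list of secondary endpoints for the interventional phase (Study endpoints) includes "Emergence of multidrug-resistant organisms (MDRO) until day 90". The Background presents the trial as the "first trial worldwide looking into the effects of synbiotics on the emergence of multidrug-resistant organisms".

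The Cultural microbiology section sets out how study samples are cultured. Of targeted culture for MDRO and pathogens of interest it says: "This needs to be assessed for every included patient in the samples from day 90". For the earlier samples it says: "In cases with detection of MDRO colonization in the day 90 samples, baseline and day 30 samples will be selected for cultural analysis", and it gives the purpose: "in order to differentiate between newly acquired and preexisting MDRO colonization".

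A day 30 stool sample is planned for all participants; the day 30 row of Table 2 (Study visits) reads "2nd questionnaire and 2nd fecal sample". Two other routes could bring an MDRO to light. The eCRF records "Detection of MDRO during any local microbiological sampling" (Electronic case reporting file). Cultural microbiology also allows that, where the cause of an infection is unclear, "samples preceding the development of an infection may be selected to recultivate the causative pathogen". The article does not say whether a finding by either route counts towards the endpoint.

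**The concern.** The label describes an event at any time between surgery and day 90. The culture rule starts from one time point at the end of that period and looks back only if that point is positive. The two agree only if every MDRO acquired after surgery is still detectable at day 90.

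What is at stake is how a difference between arms is read. A synbiotic might lower the chance of acquiring an MDRO, shorten carriage once acquired, or both. Under this rule each of these would lower the count in the same way, and study culture could not tell them apart. A result reported under the present label would invite the reading that acquisition was prevented, on a topic that the Background puts forward as new worldwide.

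**Working it through.** No figure is stated for this endpoint: the article gives no MDRO rate, effect size or power. The check is therefore one of logic, followed by a short illustration.

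**Step 1. Possible culture histories under the rule.** These are the true states that culture would show if all three samples were cultured for the same organism.

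| Baseline | Day 30 | Day 90 | Earlier samples cultured? | Classed by study culture as | Acquired by day 90? |
|---|---|---|---|---|---|
| − | − | − | no | no emergence | none seen in any sample |
| − | − | + | yes | new | yes |
| − | + | + | yes | new | yes |
| − | + | − | no | **no emergence** | **yes** |
| + | either | + | yes | pre-existing | no |
| + | either | − | no | no emergence | no |

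The classification departs from the label in one row: negative, positive, negative. The sample that would show the acquisition is planned (day 30, collected on days 28–49) but is not routinely cultured.

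**Step 2. What the rule estimates.** Among patients negative at baseline, let a be the risk of acquiring an MDRO by day 90 and c the share of those acquisitions no longer present at day 90. Then

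observed risk = a × (1 − c)

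and, with subscript 1 for synbiotic and 0 for placebo,

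observed risk ratio = [a₁ × (1 − c₁)] / [a₀ × (1 − c₀)].

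**Step 3. Equal acquisition (a₁ = a₀), so the true ratio for acquisition is 1.** The ratio reduces to (1 − c₁)/(1 − c₀). All clearance shares below are assumptions.

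| c₀ (placebo) | c₁ (synbiotic) | Calculation | Observed risk ratio |
|---|---|---|---|
| equal to c₁ | equal to c₀ | (1 − c)/(1 − c) | 1.00 |
| 0.25 | 0.50 | 0.50/0.75 | 0.67 |
| 0.30 | 0.60 | 0.40/0.70 | 0.57 |
| 0.60 | 0.30 | 0.70/0.40 | 1.75 |

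If clearance is the same in both arms, the ratio is not distorted and only the number of observed events falls. If clearance differs, an apparent effect on emergence can arise with no effect on acquisition, in either direction.

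**The case against.** The strongest reply is that the rule is a deliberate, openly described way of saving laboratory work, and that it does more than count carriers at day 90. This is right. A reader might infer that the trial measures plain carriage at day 90, but the text does not support that: baseline samples of day 90 positives are cultured precisely to separate new from existing colonisation.

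A reader might also infer that every cleared acquisition is lost. That goes too far. MDRO found in local clinical sampling are entered in the eCRF by plan, and samples preceding an infection may be cultured. Still, the first route depends on a clinical reason to sample and the second is optional. Neither would systematically find silent carriage, and neither is tied to the endpoint.

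Three further inferences do not hold:

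- *That patients without a day 90 sample are a gap in the plan.* An article commonly leaves such handling to the full protocol or laboratory documents. The assumed 25% drop-out is defined on the GIQLI score and says nothing about stool samples.
- *That unknown baseline status in day 90 negatives invalidates the comparison.* Randomisation balances baseline colonisation in expectation, so comparing new colonisation at day 90 among all sampled patients is a valid contrast.
- *That a definite amount of power is lost.* The article gives no rates from which to calculate it and claims no power for this endpoint.

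It is also fair to say that culturing all three samples would still miss anything acquired and cleared between two sampling points. That makes full culture a matter of degree. It does not close the gap between the present label and the present rule.

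**Conclusion.** The point holds as a mismatch between a named endpoint and the rule that measures it. Study culture identifies newly acquired MDRO colonisation still present at day 90. It does not identify all emergence up to day 90, and it cannot separate fewer acquisitions from faster clearance. This follows from the text alone and needs no assumed rate.

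The size is unknown. It depends on how many acquisitions clear before day 90 and on whether clearance differs between arms, and the article informs neither. The ratios of 0.57 to 1.75 show what differing clearance could do under assumed figures; they are not predictions. If few acquisitions clear by day 90, the mismatch has little numerical effect.

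The consequence is limited. The Statistical analysis plan section treats every result other than the primary endpoint as exploratory, so the confirmatory test and the sample size are untouched. The Background claims novelty of topic and not a finding, so misreporting is a risk and not something the document has already done. The mismatch is still worth correcting, because the label decides what the trial may conclude on this outcome.

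**What to change.** Restate the endpoint as *newly acquired MDRO colonisation present at day 90 (day 90 culture positive, baseline culture negative)*, and limit the conclusion to that quantity. Report MDRO recorded in the eCRF from local clinical sampling separately, and say that they do not enter this endpoint.

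The cost is a change of wording and a narrower claim on an exploratory endpoint. It needs no additional cultures, because the existing rule already delivers the restated quantity. The first participant was included in September 2025 and recruitment is planned over 2–3 years, so the wording can be settled well before analysis.

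Culturing baseline and day 30 samples for everyone would bring the measurement closer to the present label, at the price of more laboratory work. That is an optional resource choice and is not needed for the correction.

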#### Whole genome-sequencing of selected isolates

Selected isolates both from study samples and infection-related samples might be subjected to whole genome sequencing. Briefly, sequencing libraries and sequencing might be performed using state of the art library preparation kits and sequencers (Illumina) followed by de novo assembly using suitable software (i.e. Velvet). Assembled genomes may then be used for comparison i.e. using cgMLST and traditional 7-loci MLST using SeqSphere+ software version 6.0.2 (Ridom, Münster, Germany). Furthermore, presence of resistance genes will be determined.

#### Microbiota analysis

Microbiota analysis of selected samples will be performed at the central laboratories of University Hospital Tübingen for fecal samples. Briefly, genomic DNA will be extracted from samples using suitable extraction kits (i.e. FastDNA Spin Kit for Soil for fecal samples, Biomedicals, Solon, OH, USA). Concentration and quality of the extracted DNA will be assessed spectrophotometrically (Nanodrop One, Thermo Fisher Scientific, Waltham, MA, USA) and the amount of double-stranded DNA will be quantified using the Qubit dsDNA kit (Thermo Fisher Scientific, Waltham, MA, USA). Libraries for shotgun metagenomic sequencing will be prepared using suitable protocols (e.g. adaptor-ligation using the NEXNext Ultra II FS DNA Library Prep kit and NEBNext Multiplex Oligos for Illumina (New England Bioabs, Ipswich, MA, USA)), followed by sequencing using the NovaSeq 6000 platform (Illumina, San Diego, CA, USA) to allow for cost efficient ultra-deep sequencing of the samples (up to 8.2B 2 × 150 base pairs per sample/ 5.9 Gb per sample). In selected cases, sequencing may be additionally performed on a long-read sequencing platform (i.e. PromethIon).

For data analysis, suitable bioinformatics platforms and approaches will be applied to achieve taxonomic classification (i.e. Kraken2, Kaiju, DIAMOND/MEGAN) and functional pathway profiling (i.e. using HUMAnN 2.0).

#### OLINK^®^ Target 48 Cytokine and Target 48 Immune Surveillance panels

Staff of the laboratory of the Department of Clinical Epidemiology of Early Cancer Detection of the German Cancer Research Center (DKFZ) will pipet 10 µL serum on plates provided by the company OLINK, Uppsala, Sweden. The plates will be used to measure the OLINK^®^ Target 48 Cytokine and Target 48 Immune Surveillance in the core facility of the DKFZ, which will lead to the measurement of 89 unique proteins with absolute quantification, which are relevant for immune function and inflammation.

#### Metabolomics

A pre-defined set of metabolomic biomarkers (amino acids, fatty acids, and bile acids) will be measured with targeted Gas or Liquid Chromatography-Tandem Mass Spectrometry (GC-MS/MS or LC-MS/MS) in fecal and plasma samples collected prior surgery and 90 days after surgery at the metabolomics platform of the NCT Dresden, which will ensure high accuracy by using acknowledged standards for the metabolites. Furthermore, an untargeted LC-MS/MS approach will be applied with the same samples at the metabolomics platform of the NCT Dresden, which will lead to a high number of measured metabolites (~ 3,000) but with lower accuracy because no standards for specific metabolites will be used.

Incompliance: Defined as intake of trial drugs on less than 80% of the treatment days (i.e., < 67 days) as documented in the patient diary. If no patient diary was sent back to the coordinating center, this also counts as incompliance.Late completion of the day 90 questionnaire: Defined as > 115 days after surgery.Use of probiotic product in addition to the study medication (i.e., any time between post-surgery and day 90 visit).Late noticed false inclusion in the trial (inclusion criteria not fulfilled or exclusion criterion was present).

All secondary endpoints with a continuous scale will be analyzed with the same statistical methods as described for the primary endpoint above, with a linear regression model adjusting for center and the baseline value of the endpoint (if accessed). The dichotomous secondary endpoints will be tested with a logistic regression model or Cox proportional hazards regression model (depending on the nature of the endpoint) adjusted for center. In addition, a generalized estimating equation (GEE) model will be applied for all outcomes that have been repeatedly assessed.

The following a priori defined subgroup analyses will be conducted (The definition of pre-operative is “Assessed at pre-surgery visit,” and the definition of peri-operative is “Ascertained between pre-surgery visit and day 90 visit”):

Age (< 65 / ≥ 65 years).Sex (female/male).Pre-operative cancer stage (I or II / III / IV).Tumor location (left colon / right colon/rectum).Pre-operative frailty (Non-frail / pre-frail / frail, as assessed with FRAIL scale [27])Post-operative stoma (no/yes, on day 30 only / yes, on day 30 and 90).Peri-operative antibiotic treatment (no (except single shot) / yes (additional to single shot)).Long-term post-operative antibiotic treatment (< 10 / ≥ 10 days).Adjuvant chemotherapy and/or radiotherapy (no/yes).Post-operative chemotherapy (no/yes, but not in week prior day 90 questionnaire date / yes, and in week prior day 90 questionnaire date).Post-operative radiotherapy (no / yes, but not in the week prior to the day 90 questionnaire date / yes, and in the week prior to the day 90 questionnaire date).Pre-operative GIQLI score (≤ median / > median).Pre-operative physical activity (≤ median / > median recorded with the Rapid Assessment of Physical Activity questionnaire (RAPA) [33]).Pre-operative alcohol consumption (Abstinent/ Alcohol consumption ≤ median / Alcohol consumption > median by grams of ethanol per week).Pre-operative smoking (current smoker / current non-smoker).Pre-operative Healthy Lifestyle Score (0–2 / 3–5 points [32])Pre-operative BMI (< 23 / 23–30 / > 30 kg/m²).Pre-operative cachexia (yes/no, definition of Blum et al. based on current BMI and weight loss in the last 6 months [35])Weight change from pre-surgery visit to day 90 questionnaire (≤ median / > median ∆BMIpct).Post-operative dietary fiber intake (≤ median / > median recorded with the validated FiberScreen 18-item food frequency questionnaire at day 90 [34])

Because of the multiplicity of tests for subgroup and secondary outcome analyses, all results except for the primary endpoint will be regarded as exploratory and not confirmatory.

No interim analyses are planned.

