#### Intervention

The intervention group will receive a commercially available probiotic and prebiotic preparation for daily use for 12 weeks, i.e., 84 days, starting on the first day after surgery, at which oral liquid diet is being tolerated (Day 1–3 post surgery).

The probiotic treatment is Essential-Biotic^®^ Complete delayed-release capsules (Allergy Research Group, CA, USA), which shall be taken once daily. One capsule contains 50 billion colony-forming units (CFU) of 12 different bacterial strains from the Bifidobacterium, and Lactobacillus families, as well as Streptococcus thermophiles.

Multiple-strain probiotics have been suggested to be more effective than single-strain probiotics [22]. The amount of 50 billion CFU probiotic cells is in the middle of the used probiotics of previous trials, which ranged from 3 to 100 billion CFU in most studies [23]. The current literature provides no evidence of an increased risk of complications with probiotics supplementation in humans [6].

The prebiotic treatment is 10 g/day of the fermentable fiber inulin made from chicory plants (Orafti^®^ Synergy1 powder, BENEO GmbH, Mannheim, Germany). This dose is the median dose of 10 previous trials using inulin as part of a synbiotic and administered to patients after oncologic surgery [23]. The coordinating center will fill the daily doses in sachets, whose powder content shall be dissolved in a drink by the study participants. The drink shall be used to swallow the capsule with the probiotic after a meal to reduce the contact with gastric acid.

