Flatulence is a common and dose-dependent adverse event of inulin doses ≥ 5 g/day but a tolerance was observed after 2 weeks of use, presumably by microbiota adaptation to the increased fiber availability [24]. To exclude a risk of flatulence during the wound healing phase in the first 4 weeks after surgery, inulin intake will start from week 5 on. The inulin treatment shall start in week 5–6 with 3 g/day, which is the minimal possible dose with a shown effect on microbiota abundance while there is no risk of flatulence, and be continued with 5 g/day in week 7–8 when tolerance towards the very low dose of 3 g is achieved [24]. After intake of 7 g/day in week 9–10, the full dose of 10 g/day shall be applied in week 11–12. The chosen prebiotic and probiotic will act together as a synbiotic because inulin is a specific substrate for the bacteria of the Bifidobacterium family and, to a lesser extent, the Lactobacillus family [18, 25].

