#### Day 90 visit (Day 87–108 post surgery)

The 3rd questionnaire and fecal sample collection kit will be mailed to the study participants by the coordinating center on Day 87 post-surgery, which is the last possible day trial drugs could be used (84 days of treatment + start up to 3 days after surgery). The study participants are being asked to send back the filled questionnaire and the stool sample to the coordinating center by mail in a prepaid return envelope. In addition, the study participants will be asked to send the patient diary to the coordinating center with a prepaid return envelope. Furthermore, they will be asked to donate the 2nd blood sample (38.6 ml). Depending on the distance between the patient’s home and the clinic that recruited them, they will be asked to donate this blood sample either in the clinic or to their general practitioner. In the latter case, all necessary materials will be sent from the coordinating center to them by mail.

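### The per-protocol compliance rule applies one day count to two products with different schedules, so it does not secure 80% intake of the powder, and its 67-day limit is one day short of 80%

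*Protocol article*

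**What the plan says.** The protocol article, section Statistical analysis plan, adds a per-protocol analysis as a sensitivity analysis to the modified intention-to-treat analysis. Its first exclusion criterion is incompliance: "Defined as intake of trial drugs on less than 80% of the treatment days", with the conversion "i.e., < 67 days) as documented in the patient diary". A diary that is not returned also counts as incompliance.

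The section Intervention describes a "probiotic and prebiotic preparation for daily use for 12 weeks, i.e., 84 days". The capsule is a product "which shall be taken once daily" over the whole period. The powder starts later: "inulin intake will start from week 5 on". Under Control, the placebo arm receives a matching capsule and a matching powder, so the same rule applies to both arms.

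The section Patient diary asks participants to record intake of the trial drugs. It does not say whether capsule and powder are recorded separately.

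**The concern.** The rule counts days on which trial drugs were taken, but the number of products due on a day changes from one to two at week 5. A single threshold on days therefore does not translate into the same threshold for each product. The article also does not say whether a day counts when only one of two scheduled products was taken.

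A per-protocol set is meant to contain participants who took the treatment broadly as planned. Here the treatment is a synbiotic, and the prebiotic part is given only in the later weeks. If the rule admits participants with well under 80% of the powder, or none of it, the set does not represent the combination it is meant to describe. Two analysts could also build different sets from the same diaries.

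The percentage and the day count in the same sentence also do not agree exactly.

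**Working it through.** **Inputs**
- Treatment period: 84 days (Intervention).
- Capsule: once daily, so 84 scheduled days (Intervention).
- Powder: weeks 5–12, so 8 × 7 = 56 scheduled days; weeks 1–4 are 4 × 7 = 28 capsule-only days (Intervention).
- Limit: below 80% of treatment days, stated as fewer than 67 days (Statistical analysis plan).

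**Step 1. Reproduce the stated day count.** 0.80 × 84 = 67.2, which rounds to the stated 67. The denominator is therefore the 84 days of the whole treatment period.

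**Step 2. Compare percentage and day count in whole days.**
- 66/84 = 78.6%: incompliant by both.
- 67/84 = 79.8%: incompliant by the percentage, compliant by the day count.
- 68/84 = 81.0%: compliant by both.

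The two limits disagree for exactly one value, 67 days. The day count that matches the percentage is fewer than 68.

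**Step 3. What the limit implies for the powder under each way of counting a day.**

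| A day counts if… | Consequence |
|---|---|
| both products were taken | At most 56/84 = 66.7%, so nobody could comply. This reading is impossible. |
| everything scheduled for that day was taken | 28 capsule-only days leave 67 − 28 = 39 powder days needed; 39/56 = 69.6%. With no powder: 28/84 = 33.3%, incompliant. |
| any one product was taken | 84 capsule days and 0 of 56 powder days give 84/84 = 100%, compliant. |

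Two readings are workable. Under the stricter one, about 70% of the powder is enough; under the looser one, none is needed. Neither secures 80%.

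**Step 4. Does correcting the one-day slip solve this?** No. With 68 days, the stricter reading still needs only 68 − 28 = 40 powder days, and 40/56 = 71.4%.

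**Step 5. Thresholds per product.**
- Capsule: 0.80 × 84 = 67.2, so at least 68 days.
- Powder: 0.80 × 56 = 44.8, so at least 45 days (45/56 = 80.4%).

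**The case against.** The strongest reply is that the natural reading is the stricter one. The rule speaks of trial drugs in the plural, and the Intervention section describes capsule and powder as one act, since the drink holding the powder is used to swallow the capsule. On that reading a participant without powder reaches only 33.3% and is excluded. This is a fair point: a reader might infer that the plan classes a participant with no inulin as compliant, but the article does not say so, and it follows only if any one product counts. The 69.6% figure, however, arises under the stricter reading itself.

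The Patient diary section adds that unclear compliance leads to a telephone call and, if still unclear, is treated as incompliance. That deals with unclear records, not with how a clearly recorded day is counted.

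A counting rule per product may exist in the full protocol or analysis plan, which are not shown. The point here is the numeric limit that the article does fix, which would have to match any such rule.

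Two stronger readings should not be drawn:
- A reader might object that someone who stops after treatment day 67 passes without reaching the weeks 11–12 dose step, which begins on day 71. That is a feature of any 80% rule, not a contradiction. The per-product limit does not remove it: stopping after day 28 + 45 = 73 still passes and misses 84 − 73 = 11 of those 14 days.
- A reader might see a contradiction between the visit window, "Day 87–108 post surgery", and the limit for a late questionnaire, more than "115 days after surgery". The first is a planned window and the second an exclusion limit. A tolerance of 115 − 108 = 7 days is plausible for forms returned by post. At most, the article should say that days 109–115 are a deliberate tolerance.

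**Conclusion.** The concern holds in a limited form. The stated limit does not secure 80% intake of the powder under either workable reading: the minimum is 39 of 56 days (69.6%) if everything scheduled must be taken, and 0 of 56 if any one product suffices. The article does not settle which applies, so the per-protocol set is not uniquely defined. The conflict between 80% and 67 days is real but minor, because it concerns only participants with exactly 67 recorded days.

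This rests on taking the schedule as 84 capsule days and 56 powder days, both derived from the Intervention section. How many participants would be reclassified cannot be estimated, because the article gives no expected pattern of intake.

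The consequence is confined to a sensitivity analysis. The modified intention-to-treat analysis, the 154 participants to be analysed and the 206 to be randomised are unaffected.

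**What to change.** Define per-protocol compliance separately for each product and identically in both arms, as intake on at least 80% of that product's scheduled days: capsule (verum or placebo) on at least 68 of 84 days and powder (inulin or maltodextrin) on at least 45 of 56 days, with both conditions required. This also removes the mismatch between the percentage and the day count.

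Confirm now that the diary records capsule and powder separately. The article reports the first inclusion in September 2025, and intake per product cannot be recovered later from a diary with one combined entry. If the diary does not separate them, add a column.

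The cost is a change of wording, possibly one extra diary column, and a somewhat smaller per-protocol set. A sentence stating that questionnaires from days 109–115 are accepted as a deliberate tolerance, if that is the intention, could be added at the same time.
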